### 2.2. Participants

The study is performed at two study centers, one in Germany and one in Israel. Participants of the CTRL and LBP group are recruited via the University Outpatient Clinic of the University of Potsdam, Germany. Participants with MS are recruited within the Multiple Sclerosis Center, Sheba Medical Center, Tel Hashomer, Israel. For the rational of a feasibility study a sample size of 12 participants per group is intended [43]. Participants (all sexes) aged between 18 and 65 years are included into this study. Participants eligible for CTRL group are healthy asymptomatic adults, with absence of any acute or chronic LBP. Asymptomatic participants with acute infections, pregnancy, or structural changes of the spine with or without neurological signs contra-indicating physical activities are excluded. Participants eligible for the LBP group need to report a minimum of 3 low back pain episodes within the last 12 month (not exclusively within the last 3 month) and report an average pain score of 3 or above on the numeric rating scale (NRS) within the last 3 months (NRS: numeric rating scale; 0: no pain; 10: worst imaginable pain). People with acute low back pain which occurred for the first time within the last 7 days, acute infections, pregnancy, or structural changes of the spine, with or without neurological signs contra-indicating physical activities are excluded. Participants eligible for PwMS and PwMS_STD_ group need a neurologist-confirmed diagnosis of definite MS according to the revised McDonald criteria, a score of <4.5 on the Expanded Disability Status Scale (EDSS), the ability to walk an equivalent of at least 500m without a walking aid and to be relapse-free for at least 90 days prior to testing. People with MS with cardiovascular disorders, respiratory diseases, the use of steroids or fampridine or other conditions contra-indicating physical activities are excluded.

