### 2.4. Assessments/Procedure

#### 2.4.1 Experimental procedure

Potential participants learn of this study through personal contact, e-mails and printed advertisements posted at the two centers. The study team’s contact details are provided to enable interested participants to further enquire and participate in the study. Interested participants are provided with an information pack describing the study, supported by verbal information. They are screened for eligibility according to the pre-specified inclusion and exclusion criteria at the above-mentioned study sites. With inclusion criteria met, written informed consent of the participants are obtained. Group assignment is randomly performed where applicable by the principal investigators based on a generated list matched by age and gender. The randomization list is kept concealed (password protected, exclusively accessed by principal investigator) until intervention assignment. Only data analysts remain blinded to group allocation. Prior to the baseline measurement, participants undergo a physical examination (self-reported anamneses: verified diagnosis; current pain level, complaints and impairments; musculoskeletal/orthopedic examination) by a physician to rule out contraindications that restrict or prevent participation in regard to testing and exercise intervention. Baseline measurements (M1) are conducted three days before the first training session, comprising: (1) blood sampling, (2) self-reported questionnaires, (3) mobility, (4) balance and (5) strength testing. All participants, irrespective of group allocation, perform the test battery. Additional blood sampling is conducted immediately before and three days after the first training session in order to assess the acute reaction to the initial training bout. The follow-up measurement (M2) is conducted three days after the last training session. The follow up assessment session includes tests identical to those collected at baseline, with the addition of participant rating scores of the intervention program (5-point Likert-Scale regarding exercise selection, time effort and required equipment).

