### 2.5 Outcome parameters

#### 2.5.1 Primary outcomes

The feasibility of the eccentric training program in people with low back pain and MS is evaluated by means of quantitative and qualitative measures in regard to the practical aspects of study conduction, the measurement setup and procedure and the performance of the intervention program. To evaluate the study process, recruitment rate, retention and drop-out rates will be assessed. Compliance and adherence of the participants to the eccentric exercise program are based on the training log, detailing a) how many sessions are done per week, b) which exercises are performed, c) at which intensity is trained (RPE via Borg Scale) and d) whether exercises are modified. Adverse events throughout the intervention period are documented to evaluate the safety of the program. Additionally, a subjective rating (5-point Likert-Scale) of the participants on the question whether the exercise program can be realized in a good manner regarding the exercise selection, the required time and materials is used to evaluate the feasibility of the implementation.

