#### 2.5.2 Secondary outcomes

Besides the primary outcomes on study feasibility, additional surrogate parameters, such as preliminary assessments of possible intervention effects on overall health status, mobility, and postural control as well as muscle strength, are derived. Changes in the surrogates from baseline to follow-up assessment are considered and form the basis for future multi-center investigations on the efficacy of the eccentric training program. Further, the amount and type of missing data in the specific population groups are evaluated to identify possible bias during the measurement and intervention procedure. All outcome parameters are listed in **Table 1**.

**Table 1 pone.0270875.t001:** Feasibility and surrogate outcomes of the pilot intervention study.

Feasibility Outcomes	Surrogate Outcomes
**Study process:** • recruitment rate • retention rate • drop-out rate **Compliance and adherence:** • performed sessions [N] • adaptations to exercise selection and exercise modification [comments] • exercise intensity: RPE [Borg scale; 6–20] **Safety:** • adverse events [N] • pain [NRS, 0–10] • muscle soreness [NRS, 0–10] **Program evaluation:** • exercises, time, material [5-point Likert-scale]	**Questionnaires:** • EQ-5D • CPG (only LBP) • SF-36, MSWS-12, MFIS, FES-I (only PwMS) **Mobility:** • TuG [s]; 5-STS [s] • 2min-walk test [m] (only PwMS) **Postural Control:** • COP sway length [mm] for bi- & uni-pedal stance **Strength:** • peak torque [Nm] knee flex/ext • peak torque [Nm] trunk flex/ext (only LBP) **Blood Samples:** • creatine kinase • myoglobin • C-reactive protein • interleukins (IL-6, IL-8, IL-10, IL-1β, IL-1ra, IL-4) • tumor necrosis factor-alpha

RPE: rating of perceived exertion; NRS: numeric rating scale; EQ-5D: Questionnaire developed by the EuroQol Research Foundation to assess health status; TuG: Timed Up and Go test; 5-STS: Five-times Sit-to-Stand test; CPG: Chronic Pain Grade questionnaire; SF-36: Short Form 36 Health Survey; MSWS-12: 12-item Multiple Sclerosis Walking Scale; MFIS: Modified Fatigue Impact Scale; FES-1: Falls Efficacy Scale–International.

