### 2.6 Dta management and statistics

Identifying data of the participants will be recorded once after their inclusion into the study and kept separately from all other study documents. The collected data will be pseudonymized. Documentation and storage of the measurement data takes place on password-protected, department/clinic-internal computers as well as on a web-based documentation form in accordance with the applicable data protection regulations of both countries. All study documents are locked at all times in office spaces only accessible to study team members.

Data of feasibility and surrogate outcomes are analyzed descriptively considering measures of frequency, central tendency, and distribution. The eccentric intervention program will be considered feasible when 70% of the participants adhered to two-third of the training sessions and performed the second measurement after the intervention period [59–62]. To allow conclusions about the potential efficacy of the intervention program only participants that adhered to prescriptions of the exercise program are included in the comparison of baseline and follow-up assessments. Prior to any data analysis plausibility and range checks will be carried out. A per protocol approach is used in the pilot investigation even though an intention-to-treat approach will be preferred for future investigations on the effectiveness of eccentric exercise programs. Possible intervention effects on: patient reported outcomes, mobility, postural control, strength, and muscle-metabolism as well as inflammatory markers are tested by a two-way repeated measures ANOVA (within factor: time, between factor: group allocation). If the variance analysis indicates interaction effects, post hoc testing with respective Bonferroni correction is applied to identify group differences depending on measurement time points. Effect sizes associated with univariate F-statistics will be expressed as eta-squared (η^2^) and effect sizes based on a difference in mean scores will be expressed as Cohen’s d. Study results are planned to be communicated via peer-reviewed international journal publications.

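### The programme rating, a primary feasibility outcome, has M2 as its only stated collection point, so participants who stop early and miss M2 have no stated route to give it

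*Protocol article*

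**What the plan says.** Section 2.4.1 says that the follow-up session repeats the baseline tests "with the addition of participant rating scores of the intervention program", scored on a 5-point Likert scale for the choice of exercises, the time needed and the equipment. On timing, it says: "The follow-up measurement (M2) is conducted three days after the last training session". The text names no other occasion for the rating.

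Section 2.5.1, on primary outcomes, lists "a subjective rating (5-point Likert-Scale) of the participants on the question whether the exercise program can be realized in a good manner" as the measure of whether the programme can be implemented. Table 1 (section 2.5.2) shows it as programme evaluation, one of four feasibility domains beside study process, compliance and adherence, and safety.

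Section 2.6 calls the programme feasible when 70% of participants "adhered to two-third of the training sessions and performed the second measurement after the intervention period". It says that feasibility outcomes are analysed descriptively.

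Other provisions bear on people who stop. Retention and drop-out rates are primary outcomes (2.5.1). Early termination after adverse effects is foreseen (2.3.3). How much data are missing in each population, and of what kind, is to be examined for possible bias (2.5.2).

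**The concern.** The rating asks whether the exercises, the time and the materials were workable. A participant who finds them unworkable is a natural candidate to stop, and stopping may remove the rating. The people who answer could then be selected on something close to what the question measures.

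The protocol's own reasoning supports this link. Its Discussion names limited physical capacity, inexperience with intense exertion, and limited facilities and equipment among possible reasons why adults are not active enough. It also argues that a programme must fit daily life if people are to adhere to it.

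At stake is how one primary outcome is read. A pilot meant to inform larger trials would report acceptability among M2 attenders, and could lack the opinions most useful for changing the programme.

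**Working it through.** The protocol gives no figure for this point that could be reproduced. What can be worked out is how many ratings could be absent under its own feasibility rule, and how far that could move the result.

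**Inputs from the protocol**
- Group size: "For the rational of a feasibility study a sample size of 12 participants per group is intended" (section 2.2). Three groups do the eccentric programme, so 3 × 12 = 36.
- Threshold: 70% must meet the adherence condition and complete M2 (section 2.6). The text does not say whether this applies per group or pooled, so both are shown.

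**Assumed inputs**
- Higher scores mean better acceptability.
- The gap between the completers' mean C and the mean D that dropouts would have given is 0.5, 1, 2 or 3 points.
- The favourable share among completers is 80%, 90% or 100%.

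**Step 1: largest unrated number compatible with a feasible result**
- n = 12: 0.70 × 12 = 8.4, so 9 are needed and 12 − 9 = 3 may be absent; 3/12 = 25%.
- n = 36: 0.70 × 36 = 25.2, so 26 are needed and 36 − 26 = 10 may be absent; 10/36 = 27.8%.

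These are upper bounds. They hold only if everyone who fails the rule fails it by missing M2. Someone who attends too few sessions but comes to M2 can still rate.

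**Step 2: effect on the mean rating**

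With m unrated out of n, the mean over all starters is [(n − m)C + mD]/n = C − (m/n)(C − D). The completers' mean is therefore too high by (m/n)(C − D).

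| Assumed gap C − D | 3 of 12 unrated | 10 of 36 unrated |
|---|---|---|
| 0 | 0 | 0 |
| 0.5 | 0.13 | 0.14 |
| 1 | 0.25 | 0.28 |
| 2 | 0.50 | 0.56 |
| 3 | 0.75 | 0.83 |

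With m = 0 the bias is zero whatever the gap.

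**Step 3: effect on the favourable share, worst case**

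If a share F of completers is favourable and no dropout would be, the share over all starters is F × (n − m)/n.
- n = 12: 80% becomes 0.80 × 9/12 = 60%; 90% becomes 67.5%; 100% becomes 75%.
- n = 36: 80% becomes 0.80 × 26/36 = 57.8%; 90% becomes 65.0%; 100% becomes 72.2%.

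**Step 4: does the 70% rule absorb the problem?**

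The rule has two components: sessions attended and M2 performed. The rating is not one of them. A person without M2 counts against feasibility, so dropouts lower that result. The rule is therefore not inflated, but it does not correct the rating either.

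**The case against.** The strongest reply is that this rests on what a condensed article leaves out. An exit contact, or a rule on denominators, could be in the full protocol or analysis plan, and the schedule in Figure 1 is not available here. That limits how firmly one can say that dropouts go unasked. It does not remove the point, because section 2.4.1 does state when the rating is taken, and that occasion is one which some participants may miss.

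A reader might infer that dropouts never rate the programme. The text does not support that. Nothing bars early stoppers from M2, and section 2.6 treats session adherence and M2 as separate conditions. What stands is that those who do not come have no stated route.

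A reader might also infer that acceptability is necessarily biased upward. The direction follows only for those who leave because of the programme. A relapse, an illness or a scheduling conflict need not go with a poor opinion, and the bias is zero if nobody drops out.

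Nor is the pilot's feasibility decision compromised, since the rating has no threshold and does not enter the 70% rule.

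Existing safeguards help in part. Exertion, pain and soreness are recorded at each session, modifications and adverse events are documented, and drop-out and missing data are reported. A person who stops because of pain would leave some trace. None of these records gives a participant's judgement of the time or materials, and describing missing ratings does not recover them.

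**Conclusion.** The point holds in a limited form. If the plan is followed as written, a primary feasibility outcome is obtained from M2 attenders only, and attendance is plausibly related to what the rating measures. At most 25% of a group, or 28% of the three training groups together, could be unrated while the programme still counts as feasible.

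The overstatement of the mean at that upper bound is 0.13 to 0.75 points per group for gaps of 0.5 to 3 points. It shrinks in proportion with fewer dropouts. These gaps are assumptions; the protocol gives no basis for choosing among them.

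The conclusion concerns the interpretation of the acceptability rating. It is worth correcting because the remedy is small and the opinions at risk are those a pilot most needs.

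**What to change.** In sections 2.4.1 and 2.5.1, add that any participant in groups A to C who stops training or misses M2 is asked, by phone or e-mail at that time, the same three Likert items and the main reason for stopping.

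In section 2.6, add that:
- the rating is reported with the number of raters out of all who started the programme, by group;
- ratings given at M2 and at withdrawal are shown separately and combined;
- a favourable rating is defined in advance, and the share with no rating counted as not favourable is shown only as a worst-case sensitivity bound beside the observed figure. As the main analysis it would treat people who left for unrelated reasons as dissatisfied and bias the result downward.

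The cost is a few short contacts, with no added visit, blood sample or change to the intervention. Some people will not reply, so missing ratings are reduced but not abolished. The acceptability figure may turn out less favourable.

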#### 2.4.2 Common/Joint assessments

Venous blood samples are taken from an antecubital forearm vein using disposable needles and vacutainers. Blood samples are centrifuged and serum samples frozen and stored (in aliquots at -80°C) for the analysis of markers representing the muscle metabolism (creatine kinase, myoglobin) [42] and inflammatory reactions (C-reactive protein, interleukins (IL-6, IL-8, IL-10, IL-1β, IL-1ra, IL-4), tumor necrosis factor-alpha) [41] in response to eccentric exercises and standard physiotherapy care for PwMS.

The general health status is assessed with the *EQ-5D* questionnaire (Version: EQ-5D-5L) which consists of descriptive questions addressing the dimension mobility, self-care, usual activities, pain/discomfort and anxiety/depression and a visual analog scale (VAS; 0–100) for a subjective rating of their own overall current health. The health state for each dimension is thereby represented by a number of 1–5 indicating no problem, slight problems, moderate problems, severe problems or unable to/extreme problems [47, 48].

The “Timed Up and Go test” (TuG) and “Five-times-Sit-to-Stand test” (5-STS) are utilized to assess functional capacity according to strength, agility and dynamic balance during conditions of body transition (sitting to standing/standing to sitting), walking and changing directions [49–51]. The time (s) to completion of the movement task is considered. Additionally, postural control is assessed during static balance tasks incorporating bi-pedal (eyes-open and eyes-closed) and uni-pedal stance over a time period of 30s [52, 53]. Measurements of the postural sway are based on the trace of the center of pressure (COP) excursion (mm) assessed via a custom-made balance board (Wii Balance Board, Nintendo, Kyoto, Japan; modified by CSMi Computer Sports Medicine Inc., Stoughton, MA, USA). The standardized procedure for the conduction of the functional tests includes a prior demonstration by the investigator followed by a practice trial of the participant. Afterwards two performed trials are assessed.

Force capacity of the knee flexors and extensors are assessed via isokinetic dynamometry (University Outpatient Clinic—Potsdam: Con-Trex, MJ, Physiomed AG Germany; Sheba Medical Center–Tel Aviv: CSMi Computer Sports Medicine Inc., Stoughton, MA, USA) [54–56]. The isokinetic strength test of maximum voluntary contractions (MVC) is performed within a predefined range of motion of 70° (15° to 85° knee flexion) and at a motion velocity of 60°/s. Flexion and extension are performed in an alternating manner. The isokinetic protocol consists of a warm-up (10 repetitions; 50% of MVC, concentric) followed by five repetitions of concentric MVCs and a familiarization trial of five eccentric flexion/extension movements (50% MVC) followed by five repetitions of eccentric MVCs. Trials are separated by a one-minute break. For the evaluation of maximum force capacity, peak torque (Nm) and work (J) of concentric and eccentric knee flexion and extension will be considered.

#### 2.4.3 Population-specific assessments

For LBP and CTRL, pain severity in regard to low back pain is assessed by the “Chronic Pain Grade questionnaire” considering the subscales of characteristic pain intensity, pain related disability and the overall pain grade classification [57, 58].

For PwMS and PwMS_STD_ the following questionnaires will be used in addition to the common assessments mentioned above: SF 36 quality of life in MS (SF-36), 12 item Multiple Sclerosis Walking Scale (MSWS-12), Modified Fatigue Impact Scale (MFIS), Falls Efficacy Scale International (FES-I). The MSWS-12 is currently the most widely, qualitative, patient-reported outcome measure assessing the patients’ perception of the impact of MS on walking ability. The MFIS is a modified form of the Fatigue Impact Scale based on items derived from interviews with MS patients concerning how fatigue impacts their lives. This instrument provides an assessment of the effects of fatigue in terms of physical, cognitive and psychosocial functioning. The SF-36 is one of the most widely used generic measures of health-related quality of life and has been shown to discriminate between subjects with different chronic conditions and between subjects with different severity levels of the same disease. This instrument addresses health concepts that are relevant to MS patients from the patient’s perspective. The SF-36 generates eight subscales and two summary scores. The eight subscales are: physical functioning, role limitations due to physical problems, bodily pain, general health perceptions, vitality, social functioning, role-limitations due to emotional problems, and mental health. The two summary scores are the physical component summary and the mental component summary. The FES-I is a self-administered questionnaire designed to assess fear of falling in different clinical populations. The questionnaire comprises 16 items, including a range of functional activities. Individuals are instructed to rate each activity on a 4-point Likert scale, depending on how concerned they are that they might fall if they did this activity, regardless of whether they actually perform it.

For LBP and CTRL force capacity is assessed additionally for the trunk flexors and extensors. The instrumentation as well as the protocol corresponds with the strength testing at the knee. Trunk motion is set to a range of 55° (45° flexion to 10° extension) [56].

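### The Chronic Pain Grade has no settled comparison: if LBP is tested against a pain-free CTRL group that also trains, a group-by-time interaction cannot be read as an intervention effect.

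*Protocol article*

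**What the plan says.** - **Who is selected (section 2.2).** LBP participants must have had "a minimum of 3 low back pain episodes within the last 12 month" and must "report an average pain score of 3 or above on the numeric rating scale (NRS) within the last 3 months". CTRL participants are "healthy asymptomatic adults, with absence of any acute or chronic LBP". In addition, "a sample size of 12 participants per group is intended".
- **Who is measured (section 2.4.3).** "For LBP and CTRL, pain severity in regard to low back pain is assessed by" the CPG, with subscales for pain intensity, pain-related disability and overall grade.
- **When (section 2.4.1).** Eligibility is screened first. Then "Baseline measurements (M1) are conducted three days before the first training session". M2 follows three days after the last session.
- **Who is listed (section 2.5.2, Table 1).** The CPG appears as a surrogate outcome restricted to LBP.
- **What is tested (section 2.6).** Possible intervention effects on several outcome classes, patient-reported outcomes among them, are "tested by a two-way repeated measures ANOVA (within factor: time, between factor: group allocation". An interaction leads to Bonferroni-corrected post hoc tests. Differences in means are expressed as Cohen's d, with no standardiser named.
- **Who trains (section 2.1).** LBP and CTRL both follow the eccentric program. No LBP group goes without it.

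**The concern.** The two groups in which the CPG is collected are defined by opposite ends of the construct it measures. CTRL begins at or near the lowest score, so it can stay there or get worse but has almost no room to improve. It therefore cannot show what would have happened to recurrent back pain without training. It also receives the training, so it is not an untreated reference. A significant interaction would mean only that LBP scores moved and CTRL scores did not.

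At stake is the only back-pain-specific questionnaire in the trial. Section 2.5.2 says that changes in the surrogates are to inform later efficacy trials. An LBP-minus-CTRL pain effect taken as a training effect could make the next trial too small.

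**Working it through.** **1. Setting the sections side by side.** Two readings are possible.

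| Reading | Groups with CPG in the analysis | Consequence under section 2.6 |
|---|---|---|
| Section 2.4.3 governs | LBP and CTRL | The time-by-group test can be run, but the interaction does not isolate training |
| Table 1 governs | LBP only | There is no between-group factor, so the stated test cannot be run on the CPG |

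Table 1 does not settle the matter. It puts the same LBP-only label on trunk torque, which section 2.4.3 measures in LBP and CTRL, so the label may name a population loosely.

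**2. The plan's own figure.** The 12 per group rests on a cited feasibility rationale. No SD, effect size or power is given for the CPG, so there is nothing to reproduce.

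**3. How large regression to the mean could be.** The documents give the entry threshold (3) and n (12 per group). Everything else here is assumed: normal scores on the 0-10 scale, source-population mean 3 or 4, SD 2, correlation between repeated scores 0.5 to 0.8, no training effect, CTRL change exactly 0.

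The selection excess is the amount by which those admitted exceed the source mean at screening: SD × φ(a) / (1 − Φ(a)), with a = (3 − mean) / SD.

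- Mean 3: a = 0, excess = 2 × 0.798 = 1.60 points.
- Mean 4: a = −0.5, excess = 2 × 0.509 = 1.02 points.

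Expected spurious change from M1 to M2 = −(r between screening and M1 − r between screening and M2) × excess.

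| Relation of M1 to screening | Spurious LBP change (points) |
|---|---|
| M1 no closer to screening than M2 is (gap 0) | 0 |
| Gap 0.1 | −0.10 (mean 4) to −0.16 (mean 3) |
| M1 is the selection score, r with M2 = 0.8 (gap 0.2) | −0.20 to −0.32 |
| M1 is the selection score, r with M2 = 0.5 (gap 0.5) | −0.51 to −0.80 |

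**4. What the interaction test would do.** With two groups and two times, the interaction is a two-sample t-test on change scores, here with 12 per group. Simulated with CTRL change at 0:

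- In the limiting case where M1 is the selection score, the test is significant in the favourable direction in about 9% (mean 4, r 0.8) to 31% (mean 3, r 0.5) of trials, against a nominal 2.5%.
- When M1 is a separate measurement no closer to screening than M2, two-sided error is about 6% to 7%. The analytic value for normal changes is 6.2%: with no variance in CTRL the statistic has 11 degrees of freedom but is referred to the critical value for 22 (2.074), and P(|t| on 11 df > 2.074) = 0.062.

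**5. Cohen's d.** With equal n and a pooled SD, d relative to standardising on LBP is multiplied by 1 / √((1 + k²)/2), where k = CTRL SD / LBP SD.

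| k | Factor |
|---|---|
| 0 | 1.41 |
| 0.25 | 1.37 |
| 0.5 | 1.26 |
| 1 | 1.00 |

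If d uses the LBP SD, the factor does not arise.

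**The case against.** The strongest reply is that the comparison is not established. Table 1 is described as listing all outcome parameters and gives the CPG to LBP alone. Section 2.6 never names the CPG or its comparison groups. Leaving CTRL out may already be the intention. That stands to this extent: the LBP-versus-CTRL test is one reading, not a stated fact. It does not clear the plan, because on the other reading the prescribed test has no second group.

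A reader might also infer that the ANOVA is bound to show LBP improving through regression to the mean alone. The documents do not support that. Selection uses a reported three-month average plus an episode count, taken at screening. M1 is a later visit with a different instrument, and no disability threshold applies. The upper figures above require M1 to equal the selection score; with a separate M1 the mean bias can be nil.

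A reader might likewise infer that CTRL has zero variance and that d is therefore inflated by 1.41. CTRL is pain-free at entry, but it trains and pain may arise. The factor is a ceiling that also needs a pooled SD, which section 2.6 does not specify. Nor does anything say that the EQ-5D pain/discomfort item is tested on its own, so the point does not extend to it.

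Finally, the root cause is the lack of an untrained LBP group, which no choice of analysis supplies. That is correct. A within-LBP estimate still contains any regression to the mean. What it gains is that nobody is led to think CTRL has removed it.

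**Conclusion.** The point holds in a limited form. Sections 2.4.3 and 2.6 and Table 1 do not fix one coherent CPG analysis. If CTRL is the comparator, the group-by-time interaction mixes training, natural course and regression to the mean, and it cannot be reported as an intervention effect. This conclusion rests on the eligibility rules and on CTRL also training. It needs neither zero CTRL variance nor any particular correlation.

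The size of the bias is unknown. It lies between about 0 and about 0.8 NRS points under the assumed SD, means and correlations, with d inflated by at most 1.41. The simulation concerns a pain-intensity score only; the disability subscale and overall grade were not modelled.

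The practical impact is limited. Feasibility is primary, the CPG is one of many secondary surrogates, surrogates are also to be described without testing, and the feasibility criterion in section 2.6 does not use the CPG. The change is still worth making, because it costs only wording and works on either reading of Table 1.

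**What to change.** In section 2.6:

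- Exclude CTRL from any CPG test.
- Report the M1-to-M2 change in CPG within LBP with a 95% CI, standardised by the LBP baseline SD.
- Label it an uncontrolled change that may include regression to the mean and natural course, not an intervention effect.
- Use the CTRL CPG only to confirm entry status at M1 and to describe new back pain at M2.

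Then align Table 1 and section 2.4.3 with this, so that the reader can see in which groups the CPG is collected and in which it is an outcome.

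The cost is analysis wording only; no data collection or sample size changes. The downside for the sponsor is a less favourable LBP pain effect: it loses its apparent control group and, if a pooled SD had been intended, any inflation that came with it.
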